### Study Interventions

#### Intervention Group: Nurse-Led, Acceptance and Commitment–Based, Supportive-Expressive Palliative Program

The intervention comprises 5 individual 60- to 90-minute sessions delivered over 3 months. The intervention is semistructured, with the intervener trained to facilitate discussions on 5 key themes adapted from CALM therapy and informed by findings from a previous cross-sectional study and qualitative interviews exploring the illness experience and care needs of individuals with PNDs in Hong Kong [31,32]. These themes include (1) symptom control and communication with health care professionals, (2) changes in sense of self amid progressive loss of function, (3) social support and relationships with family and friends, (4) spiritual support and finding meaning and life purpose in the context of illness, and (5) fears about disease progression and planning for the uncertain future and mortality. The time devoted to each theme and the sequence in which they are addressed will depend on the salience of the patients’ concerns during the sessions. The intervention aims to encourage patients to express concerns related to their diagnosis and treatment, describe their lived experiences and emotions, and identify current challenges. On the other hand, the intervention seeks to cultivate acceptance and promote value-driven behaviors, enhancing patients’ psychological flexibility in the face of illness, thereby enhancing psychospiritual well-being. The intervener will use acceptance and commitment–based techniques such as experiential exercises, mindfulness, and metaphors to facilitate the process. The intervention outline is shown in Table 1. The intervention will be delivered by registered nurses who have received standardized training in ACT and CALM therapy and will follow a structured intervention manual. Homework exercises will be provided to encourage participants to practice skills between sessions and maintain a record of their progress. A workbook with session content, along with audio instructions for mindfulness exercises and defusion and acceptance strategies, will be provided for home practice. In each session, participants will be encouraged to share their experiences and discuss any difficulties encountered during practice to consolidate learning and troubleshoot challenges.

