#### Control Group: Befriending Activity

Participants in the control group will receive 5 individual 30- to 60-minute befriending sessions over 3 months delivered by a trained registered nurse following the *Befriending Manual* [34]. Befriending serves as an active control condition designed to control for nonspecific therapeutic factors, including clinician contact time, attention and interpersonal support (eg, warmth and empathy), participant expectations of benefit, and the therapeutic alliance. Sessions focus on neutral, everyday topics of interest (eg, hobbies, pets, and current affairs) and avoid emotional exploration, problem-solving, or therapeutic techniques. The nurse will maintain a warm, friendly, and supportive stance throughout. For pragmatic reasons, extending unstructured befriending sessions beyond 60 minutes may lead to forced or unnatural conversations, which could inadvertently increase participant fatigue or lower retention rates.

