### Data Collection Procedure

Potential participants will be provided with a general overview of the study. A research assistant will set an appointment with those patients who meet the inclusion criteria and agree to participate in the study. In the face-to-face interview, a research nurse will check the eligibility criteria and perform the baseline evaluation (T0). Information on all screened patients and reasons for exclusion will be recorded. Participants will receive a cash reward of HKD 100 (approximately US $13) per each assessment (T0, T1, and T2). To control for participant expectancy, both groups will be introduced with identical positive phrasing regarding the potential benefits of the interventions. After baseline assessment, participants will be randomly assigned to the 2 groups on a 1:1 basis using the method of permuted block with random block sizes of 4, 6, and 8 by an independent researcher not involved in the assessments. The allocation list will be computer generated by an independent researcher and concealed from other researchers and participants until the time of assignment. An independent research assistant blinded to the group allocation will collect the postintervention questionnaires. Figure 1 shows the flowchart of the study implementation plan.

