### Data Analysis

Quantitative data will be analyzed using SPSS (version 28.0.1; IBM Corp) following the intention-to-treat principle. Descriptive statistics will summarize baseline characteristics, and group comparability will be examined using chi-square or Fisher exact tests. Linear mixed-effects models will assess intervention effects on primary and secondary outcomes, with time, group, and group-by-time interaction included as fixed effects. Between-group differences will be estimated using linear contrasts. Model assumptions will be checked using normal probability plots. Missing data will not be imputed as mixed-effects models accommodate incomplete observations [48]. A 2-sided significance level of 5% will be adopted. To account for the variations in therapist contact and attention, we will log the exact duration (in minutes) of each session for every participant. In sensitivity analysis, total contact time will be included as a covariate in the linear mixed-effects models to statistically control for the potential confounding effect of extra nurse contact.

Qualitative interviews will be transcribed verbatim and managed using NVivo (version 12; Lumivero). Two researchers will independently conduct inductive thematic analysis following a 5-step approach [49]. Codes will be organized into categories and themes to identify recurring patterns. An audit trail will enhance rigor, and discrepancies will be resolved through discussion. Qualitative findings will complement and enrich interpretation of the quantitative results.

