### Limitations

This study has several limitations. First, convenience sampling from outpatient clinics and support groups may introduce selection bias and limit generalizability to less socially engaged individuals. Second, there is a risk of contamination if control group participants become aware of the intervention content. To minimize this risk, intervention group participants will be instructed not to discuss or share any aspects of the intervention content or materials with others. Third, due to the nature of the intervention, blinding of participants is not possible. Awareness of group assignments may influence participant responses, compliance, and retention rates [54]. Fourth, the discrepancy in session duration between the intervention group and the befriending control group may introduce a confounding effect related to extra nurse contact and attention. For pragmatic reasons, the befriending control is restricted to neutral, nonaffective topics lasting 30 to 60 minutes to sustain engagement, whereas CALM therapy involves a highly semistructured 90-minute framework with interactive experiential exercises. Consequently, while the active control accounts for therapist warmth and alliance, we cannot fully separate content-specific benefits from differences in total contact time. This remains a potential bias that we will attempt to mitigate by controlling for total contact time in our sensitivity analysis. To enhance adherence, participants who complete assessments will receive a modest incentive (HKD 100 [approximately US $13] per assessment).

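### Adjusting for total contact time does not control for the extra nurse contact: minutes follow from allocation, and the adjusted model is either uninformative or rests on unstated assumptions

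*Protocol article*

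**What the plan says.** The intervention section states: "The intervention comprises 5 individual 60- to 90-minute sessions delivered over 3 months". The control section states: "Participants in the control group will receive 5 individual 30- to 60-minute befriending sessions over 3 months". The control section also says "Befriending serves as an active control condition designed to control for nonspecific therapeutic factors, including clinician contact time", among other factors.

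Allocation comes before any session: "After baseline assessment, participants will be randomly assigned to the 2 groups on a 1:1 basis" (Data Collection Procedure). The main model is a linear mixed model "with time, group, and group-by-time interaction included as fixed effects" (Data Analysis). For contact, the same section says "we will log the exact duration (in minutes) of each session for every participant". As a sensitivity check on the additional time spent with the nurse, it then plans that "total contact time will be included as a covariate in the linear mixed-effects models to statistically control for the potential confounding effect".

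Limitations concedes that benefits of content cannot be fully separated from differences in contact time, and then adds: "This remains a potential bias that we will attempt to mitigate by controlling for total contact time in our sensitivity analysis". The article does not say whether minutes enter as a main effect, crossed with time, or as a time-varying covariate.

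**The concern.** A confounder is a common cause of treatment and outcome. Minutes of contact cannot be that here, because they are logged after randomisation and their range is set by the assigned arm. They are part of the treatment and a possible mediator.

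What is at stake is how a positive result is read. The obvious rival explanation is that patients improved because they had more nurse time, and this is the only analysis the article names to address it. If the model cannot change the contrast of interest, a statement that the effect persists after adjustment is empty. If it can, a vanishing effect may reflect collinearity, or a prognostic difference between people who stay and people who stop. In either case the conclusion about content versus attention would be unreliable.

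**Working it through.** **1. Planned contact (intervention and control sections).** Intervention: 5 × 60 = 300 to 5 × 90 = 450 min. Control: 5 × 30 = 150 to 5 × 60 = 300 min. With full attendance the arms share only the value 300.

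**2. Minutes as a main effect.** Write the mean for person i at visit t as α + τₜ + βgᵢ + δₜgᵢ + γCᵢ, where Cᵢ is total minutes. The change from T0 is (τₜ − τ₀) + (δₜ − δ₀)gᵢ. The term γCᵢ cancels, so the group-by-time contrasts do not depend on it. In a simulation where minutes caused the whole effect, the two contrasts were -0.506 and -0.852 both without and with minutes. In other runs the largest change was about 1e-14 in complete data and about 0.05 SD with dropout-related missing data. If the contrast is instead the group difference at a visit, adjustment shifts it at every visit, including T0, before any contact has occurred (one example: 0.17 to 0.47).

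**3. Minutes acting on change, full attendance.** Assumption: session length is uniform within each stated 30-minute range.
- Mean totals are 5 × 75 = 375 and 5 × 45 = 225. Half the difference is 75, so between-arm variance B = 75² = 5625.
- Variance of one session is 30²/12 = 75. Within-arm variance W is 5 × 75 = 375 if sessions are independent, and 25 × 75 = 1875 if each person's sessions are all the same length.
- R² = B/(B + W) = 5625/6000 = 0.94, or 5625/7500 = 0.75.
- Variance inflation 1/(1 − R²) = 16 or 4, so the standard error is multiplied by 4 or 2. A simulated mixed model with minutes crossed with time went from 0.197 to 0.744.
- Power: with d = 0.58, two-sided 2.5% and 59 per arm, unadjusted power is 0.81, in line with the planned 80%. Dividing 59 by the inflation factor gives about 0.25 (factor 4) or 0.07 (factor 16).

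**4. Minutes acting on change, incomplete attendance.** Assumptions: 15% in each arm stop early, after 0, 1, 2, 3 or 4 sessions with equal chance (mean 2, variance 2), and stoppers do k SD worse. The protocol's own 15% is attrition for sample size, not session attendance.
- Stoppers average 150 min (intervention) and 90 min (control). Difference in arm means D = 0.85 × 150 + 0.15 × 60 = 136.5, so B = 68.25² = 4658.
- W, intervention, independent sessions: 0.15 × 0.85 × 225² + 0.15 × (75² × 2 + 150) + 0.85 × 375 = 6455 + 1710 + 319 = 8484. Control: 0.15 × 0.85 × 135² + 0.15 × (45² × 2 + 150) + 319 = 2324 + 630 + 319 ≈ 3272. The average is 5878. With equal-length sessions the average is 7198.
- R² = 0.44 or 0.39; the standard error is multiplied by about 1.3.
- Pooled covariance of stopping with minutes = −0.1275 × (225 + 135)/2 = −22.95.
- Adjusted effect when minutes do nothing = −0.58 + k × 22.95 × 136.5/W, which is −0.58 + 0.53k or −0.58 + 0.44k.
- k = 0.1 gives -0.53 to -0.54; k = 0.5 gives -0.31 to -0.36; k = 0 gives no bias.
- For k = 0.5, stopping after 0-2 sessions gives -0.34 to -0.37 (R² 0.31-0.34), and stopping after 1-4 gives -0.26 to -0.34 (R² 0.47-0.54). Separate simulations gave about -0.33 to -0.38.

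**5. When the adjustment works.** In simulations with 138 participants, full attendance, no effect of minutes and no unmeasured common cause, the adjusted estimate was -0.58, with standard error 0.451 against 0.168 unadjusted. An engagement factor that lengthens contact and improves outcome by only 0.1 SD per SD moved it to -0.13 with full attendance and to -0.50 with 15% non-completion.

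**The case against.** Several points on the other side stand. This is labelled a sensitivity analysis, so the intention-to-treat estimate, sample size and hypothesis test do not rest on it. Limitations admits that content and contact cannot be fully separated and promises only an attempt at mitigation. The model form may be fixed in an analysis plan that is not shown, so the empty main-effect reading is conditional on that choice. The arms do match on number of sessions, period and nurse delivery.

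A reader might go further and infer that contact can never be adjusted for, or that any conclusion from the model must be false. The documents do not support that: step 5 shows an unbiased, though imprecise, estimate if contact acts on change and has no unmeasured common cause with outcome. A reader might also combine the near-collinearity with the bias from early stopping. These belong to different scenarios: the first needs full attendance, and the second needs people to stop, which weakens the collinearity.

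What remains is that every form either leaves the contrast as it was or relies on an assumption that randomisation does not protect and the article does not state. The concession in Limitations does not cover this, because it goes on to offer the analysis as mitigation.

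**Conclusion.** The point holds and should be fixed, but it concerns labelling and interpretation; the primary analysis is untouched. Two parts need no outside assumption: the planned totals meet only at 300 min, and a main effect of total minutes leaves the group-by-time contrasts unchanged in complete data. The remaining figures are conditional. R² of 0.75-0.94 and a two- to fourfold standard error assume full attendance and uniform session lengths. R² of about 0.3-0.5 and the shift from -0.58 assume 15% early stopping and a chosen prognostic gap. With incomplete attendance, the overlap largely sets intervention non-completers against control completers, and the bias grows with how strongly attendance tracks prognosis. The claim that befriending controls for clinician contact time is too broad, since session lengths differ by design, but this is a minor wording point.

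**What to change.** 1. In Data Analysis, remove the contact-time-adjusted model as a control for extra contact. Alternatively, keep it only as an exploratory mediation-type analysis: minutes allowed to act on change, baseline covariates included, and the assumption of no unmeasured common cause of contact and outcome written down.
2. In Limitations, delete the mitigation claim and keep the concession.
3. Use the logged data to report minutes and sessions attended by arm.
4. State that the primary comparison is the whole programme, extra contact included, against befriending.
5. In the control-group section, limit the contact-time claim to number of sessions and period, and say that minutes are not matched.

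The cost is wording and, if the exploratory model is kept, a little analysis work. Logging continues as planned. With 132 of 138 participants enrolled and no outcome data analysed as of January 2026, the change can be dated and documented before analysis.

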### Patient and Public Involvement

Patients and the public were not involved in the design, conduct, reporting, or dissemination plans of this research protocol.

### Ethical Considerations

This study complies with the Declaration of Helsinki and has received approval from the Institutional Review Board of the University of Hong Kong and the Hospital Authority Hong Kong West Cluster (UW 22-727). Participants will receive detailed verbal and written information about the study and provide informed consent. Participation is voluntary, and individuals may withdraw at any time without consequences. To ensure confidentiality, participants will be assigned unique codes, and no identifying information will appear in study materials. Data will be securely stored, accessible only to the research team, and destroyed 7 years after study completion.

### Validity and Reliability

Intervention fidelity will be monitored through random review of 10% of audio-recorded sessions by an independent researcher with prior written consent from participants. Fidelity checklists adapted from the CALM Treatment Integrity Measure [21], ACT Fidelity Measure [50], and *Befriending Manual* [34] will be used. Quantitative data will be double entered for verification and analyzed using an intention-to-treat approach. All outcome measures have established reliability and validity in Chinese populations, and internal consistency (Cronbach α) will be calculated using study data. For qualitative rigor, 2 authors will verify transcripts against audio recordings. Coding will be conducted independently, with consensus reached through discussion.

### Dissemination

The findings of this trial will be disseminated to health care professionals, researchers, and the public through peer-reviewed publications in international journals and presentations at national or international scientific conferences.

## Results

Ethics approval was obtained on December 22, 2022. The study is funded by the Nethersole Institute of Continuing Holistic Health Education (NICHE) Research Grant from March 1, 2023, to March 1, 2025, and by the Health and Medical Research Fund (HMRF) from July 1, 2024, to September 30, 2026. Prospective clinical trial registration was completed on June 30, 2023, prior to the start of recruitment and data collection in September 2023. As of January 2026, 132 participants have been enrolled. No outcome data analyses have been conducted to date. The trial results are expected to be published in late 2026.

## Discussion

### Expected Findings

The progressive and unpredictable nature of PNDs contributes to significant psychospiritual distress, including depression, anxiety, existential distress, and loss of life meaning. While conventional care primarily focuses on motor symptom management within a biomedical framework [51], psychological and spiritual needs are often underaddressed. To bridge this gap, this study developed a novel nurse-led, community-based palliative intervention integrating CALM therapy and ACT to foster acceptance, meaning, and value-driven living across the illness trajectory.

Guided by the CSM [15], the intervention targets maladaptive illness perceptions shaped by the chronic, irreversible, and unpredictable course of PNDs, which often diminish perceived control and heighten helplessness. The integration of CALM therapy and ACT within this palliative intervention specifically aims to address these issues. CALM’s supportive-expressive approach encourages patients to explore illness-related concerns and existential issues, reframe negative thoughts, and sustain hope along the fluctuating illness trajectory, whereas ACT complements this by fostering psychological flexibility—the ability to accept difficult emotions, focus on the present, and engage in value-driven behaviors. Together, these approaches empower individuals with PNDs to navigate the uncertainty and distress of PNDs while maintaining a sense of control and purpose.

The intervention underscores the pivotal role of nurses in delivering holistic, person-centered psychospiritual care in community settings. With appropriate training and standardized protocols, nurses can address emotional and existential challenges beyond physical symptom management. By integrating relational skills, empathy, and expertise in neurological care, this study demonstrates how nursing practice can extend beyond traditional hospital-based roles to include psychotherapeutic interventions that foster psychospiritual well-being. Designed to accommodate the fluctuating course of PNDs [11], the program offers flexible delivery options, including home- or site-based sessions within a 3-month period. Individual sessions provide a private, personalized space for discussing sensitive concerns and align with evidence supporting psychological approaches for psychospiritual distress in palliative populations [52,53].

This study has important theoretical and clinical implications. Theoretically, it advances understanding of how illness perceptions influence coping and psychological outcomes in PNDs within the CSM framework and extends the application of CALM therapy and ACT to chronic progressive conditions. Clinically, it demonstrates the feasibility of nurse-led psychotherapeutic interventions in community palliative care. If effective, the program could offer a scalable model for integrating psychospiritual care into routine services. Insights from participants’ experiences will further refine the intervention’s contextual relevance and support the development of innovative, evidence-based practices in psychospiritual care for individuals with PNDs.

### Limitations

This study has several limitations. First, convenience sampling from outpatient clinics and support groups may introduce selection bias and limit generalizability to less socially engaged individuals. Second, there is a risk of contamination if control group participants become aware of the intervention content. To minimize this risk, intervention group participants will be instructed not to discuss or share any aspects of the intervention content or materials with others. Third, due to the nature of the intervention, blinding of participants is not possible. Awareness of group assignments may influence participant responses, compliance, and retention rates [54]. Fourth, the discrepancy in session duration between the intervention group and the befriending control group may introduce a confounding effect related to extra nurse contact and attention. For pragmatic reasons, the befriending control is restricted to neutral, nonaffective topics lasting 30 to 60 minutes to sustain engagement, whereas CALM therapy involves a highly semistructured 90-minute framework with interactive experiential exercises. Consequently, while the active control accounts for therapist warmth and alliance, we cannot fully separate content-specific benefits from differences in total contact time. This remains a potential bias that we will attempt to mitigate by controlling for total contact time in our sensitivity analysis. To enhance adherence, participants who complete assessments will receive a modest incentive (HKD 100 [approximately US $13] per assessment).

